## Abstract

**Background:**

Robot-assisted surgery is being increasingly adopted in treating colorectal cancer, and the transition from laparoscopic surgery to robot-assisted surgery is a trend. The evidence of the benefits of robot-assisted surgery is sparse. However, findings are associated with improved patient-related outcomes and overall morbidity rates compared to laparoscopic surgery. This induction is unclear, considering both surgical modalities are characterized as minimally invasive. This study aims to evaluate the systemic and peritoneal inflammatory stress response induced by robot-assisted surgery compared with laparoscopic surgery for elective colon cancer resections in a prospective, randomized controlled clinical trial.

**Methods:**

This study is a single-centre randomized controlled superiority trial with 50 colon cancer participants. The primary endpoint is the level of systemic inflammatory response expressed as serum C-reactive protein (CRP) and interleukin 6 (IL-6) levels between postoperative days one and three. Secondary endpoints include (i) levels of systemic inflammation in serum expressed by a panel of inflammatory and pro-inflammatory cytokines measured during the first three postoperative days, (ii) postoperative surgical and medical complications (30 days) according to Clavien-Dindo classification and Comprehensive Complication Index, (iii) intraoperative blood loss, (iv) conversion rate to open surgery, (v) length of surgery, (vi) operative time, (vii) the number of harvested lymph nodes, and (viii) length of hospital stay. The exploratory endpoints are (i) levels of peritoneal inflammatory response in peritoneal fluid expressed by inflammatory and pro-inflammatory cytokines between postoperative day one and three, (ii) patient-reported health-related quality of recovery-15 (QoR-15), (iii) 30 days mortality rate, (iv) heart rate variability and (v) gene transcript (mRNA) analysis.

**Discussion:**

To our knowledge, this is the first clinical randomized controlled trial to clarify the inflammatory stress response induced by robot-assisted or laparoscopic surgery for colon cancer resections.

*Trial registration* This trial is registered at Clinicaltrials.gov (Identifier: NCT04687384) on December, 29, 2020, Regional committee on health research ethics, Region of Southern Denmark (N75709) and Data Protection Agency, Hospital Sønderjylland, University Hospital of Southern Denmark (N20/46179).

**Supplementary Information:**

The online version contains supplementary material available at 10.1186/s12893-021-01355-4.

## Background

Laparoscopic colon surgery is an implemented and well-established surgical procedure for colon malignancies worldwide. The method was introduced in the 1990s and is associated with fewer wound-related complications, less pain, and similar pathological specimen quality compared to open colonic surgery [1–6]. However, the disadvantages of laparoscopic colon surgery include a prolonged learning curve, suboptimal ergonomics, tremor and camera position [7–9].

Within the last 20 years, robot-assisted colon surgery has become more widespread among several surgical specialities. To date, no randomized controlled trials comparing the systemic or peritoneal inflammatory response in colon cancer surgery performed by robot-assisted or laparoscopic methods has been published. A decreased systemic inflammatory response is associated with a lower risk of surgical complications and improved long-term oncological outcomes [10]. This response is due to a cascade of neuroendocrine, metabolic and immunological factors. In the systemic acute inflammatory reaction, a release of pro-inflammatory cytokines (IL-1β, IL-6 and TNF) occurs as part of wound healing by producing acute phase reactants (C-reactive protein (CRP), fibrinogen and complement C3) as a reaction to the initial surgical trauma [11, 12]. High concentrations of pro-inflammatory cytokines (predominantly IL-6) and lack of compensatory expression of anti-inflammatory cytokines may cause systemic inflammatory response syndrome (SIRS). There is a direct correlation between high concentrations of pro-inflammatory cytokines and an increased mortality rate [11, 13]. Non-randomized clinical trials have demonstrated that robot-assisted colorectal surgery has positive effects on faster establishment of bowel function and shorter hospital stay than laparoscopic surgery [14–17]. One study reported that robot-assisted surgery contributes to reduced surgical trauma due to better tissue exposure because of 3D-vision, wristed instruments and tremor reduction minimizing the inflammatory stress response, compared to the laparoscopic method [18].

This study aims to evaluate the systemic and peritoneal inflammatory stress response induced by robot-assisted surgery compared with laparoscopic surgery for elective colon cancer resections in a prospective, randomized controlled clinical trial.

## Methods/design

### Study design

A single-institution double-blinded randomized controlled trial was conducted at the tertiary care hospital (Surgical Department, Hospital Sønderjylland, University Hospital of Southern Denmark, Denmark) with participants requiring colon surgery for malignancy. The study protocol adheres to the guidelines determined in Standard Protocol Items: Recommendations for Interventional Trials (SPIRIT) [19].

#### Inclusion criteria

Elective robot-assisted or laparoscopic surgery for right-sided, left-sided and sigmoid colon cancer.Age ≥ 18.ASA-score ≤ 3.Tumor-stage (T1–T4a).Endoscopic suspected colon cancer.Histologically verified adenocarcinoma, signet ring cell carcinoma, undifferentiated cancer, medullary carcinoma or another malignant tumour type originating from the colon.Patients must give written informed consent.Patients must be able to understand Danish.

#### Exclusion criteria

Carcinoma of the transverse colon or synchronous colorectal cancer.Previous history of any colon resection.Previous open major abdominal surgery except for open appendectomy and cholecystectomy.Pregnancy.Metastatic disease.History of psychiatric or addictive disorder that would prevent the patient from participating in the trial.Emergency colon surgery.Co-existing inflammatory bowel disease.Co-existing immunological disease requiring ingestion of systemic immunomodulatory drugs (DMARD—disease-modifying anti-rheumatic drugs) - uploaded as Additional file 1, corticosteroids and/or biologic disease-modifying anti-rheumatic drugs.Daily consumption of NSAID drugs.

### Interventions

#### Surgical procedures

Patients will receive preoperatively the prophylactic antibiotics Piperacillin/Tazobactam 4 g + 0.5 g and Metronidazole 1.5 g, compression stockings and antithrombotic drugs (Dalteparin 5000 IU), urinary catheter, and a nasogastric tube. No mechanical bowel preparation will be used before surgery. According to oncological principles, a dedicated team of certified colorectal and robotic surgeons will perform all surgical procedures in an institution performing > 200 malignant colon resections yearly. Since the implementation of robot-assisted colorectal surgery in our institution in 2017, the operating surgeons' caseloads have surpassed the learning curve of 25–45 cases [20–23]. In addition, in our institution, laparoscopic colorectal resections have been performed since 2005, and the operating surgeons are familiar with these surgical techniques, surpassing the learning curve of approximately 50 cases [24]. Surgical procedures will be performed either laparoscopically or entirely robot-assisted. The robot-assisted procedures will be performed using a da Vinci Xi system (Intuitive Surgical, Sunnyvale, California, US).

#### Right-sided colectomy

In right-sided and extended right-sided colectomy, by consensus within our institution, the approach is lateral-to-medial. The transverse colon is dissected medial to lateral, proceeded by entering into the lesser sac. The gastrocolic ligament is divided, the hepatic flexure is mobilized, Toldt’s fascia is incised, and attachments to the lateral abdominal wall are dissected. The cecum is retracted cranially to expose the ileocolic pedicle. The dissection continues medially until the descending part of the duodenum and the pancreatic head are located where the gastrocolic trunk runs into the superior mesenteric vein. The ileocolic pedicle is isolated, clipped and divided individually with a sealer device at its origin. The dissection continues above the duodenum. The right colic artery and the right branch of the middle colic artery are identified and divided with a sealer device at the origin. The ileal mesentery is divided, and mobility is ensured to obtain a tension-free anastomosis. The terminal ileum and transverse colon are divided intracorporeally with a laparoscopic stapler. The specimen is extracted through a right-sided upper horizontal transverse muscle splitting incision. An extra-corporeal, hand-sewn, end-to-end, single layer, seromuscular tension-free anastomoses will be performed in both surgical modalities.

#### Left-sided colectomy

In left-sided colectomy, the approach will be lateral-to-medial. Peritoneal attachments of the lateral abdominal wall will be incised corresponding to Toldt’s fascia. The ureter is identified. The inferior mesenteric artery and vein are identified at the level of the pancreas, then clipped and divided separately with a sealer device. The dissection will continue proximally upwards toward the inferior border of the pancreas and distally to the sacral promontory. The mesocolon will be mobilized by preserving the hypogastric autonomic nerves. The gastrocolic ligament is divided, and the lesser sac is entered. The dissection is continued by division of the splenocolic ligament, and the splenic flexure is mobilized to ensure a tension-free anastomosis. The transverse colon and rectum are transected intracorporeally with a laparoscopic stapler. A muscle splitting incision is performed in the left iliac fossa, and the specimen is extracted. An extra-corporeal end-to-end hand-sewn or stapled, tension-free seromuscular anastomosis will be performed depending on tumor location and bowel length, as we prefer to perform hand-sewn anastomosis.

#### Sigmoid colectomy

The procedure is initiated by the lateral mobilization of Toldt’s fascia, including mobilization of the splenic flexure. The left ureter is identified after the completion of lateral dissection. The origin of the inferior mesenteric artery and superior rectal artery is identified. The inferior mesenteric artery and vein are clipped and divided with a sealer device. The left colon is dissected posteriorly, the pancreatic tail is identified, the greater omentum is incised to enter the lesser sac. The greater omentum is dissected medial to lateral, the splenocolic ligament is divided, and the splenic flexure is mobilized to ensure a tension-free colorectal anastomosis. The colon is divided intracorporeally, proximally and distally with a laparoscopic stapler. A muscle splitting incision is performed in the left iliac fossa, and the specimen is extracted. A stapled end-to-end colorectal anastomosis is performed. An intra-operative air leak test tests the anastomosis.

### Peritoneal microdialysis

Patients will have a 61 high cut-off microdialysis catheter (CMA 61; CMA Microdialysis AB, Stockholm®, Sweden) inserted intraperitoneally at the end of surgery. The catheter will be perfused with an isotonic perfusion fluid (Dextran) used for microdialysis, with a flow rate of 0.3 μl/min. The catheter membrane allows large molecules to diffuse into the perfusion fluid due to its permeability as it mimics a capillary [25]. Approximately 1.5 ml of intraperitoneal fluid will be collected from the abdominal cavity once daily for 3 days postoperatively.

### Postoperative management

The nasogastric tube will be removed after the cessation of anaesthesia. Both robot-assisted and laparoscopic colon surgery are categorized as minimally invasive and follow the principles of enhanced recovery after surgery (ERAS) to minimize the risk of postoperative complications, morbidity, and hospitalization time [26] and Additional file 2. Patients will be encouraged to mobilize through daily consultations with a physiotherapist. Antithrombotic treatment will continue four weeks postoperatively.

### Anesthesia and postoperative analgesic management

The operation is performed under general anaesthesia in both surgical groups and will consist of:

#### Preoperative medication

The patients will be medicated with Paracetamol (1 g × 4) and Ondansetron (4 mg).

#### Maintenance of general anaesthesia

Propofol (1–3 mg/kg) initially followed by a continuous dose of 5 mg/kg/hour.Sufentanil (0.5 μg/kg) initially followed by a continuous dose of 1,5 μg/kg.Rocuronium (0.6 mg/kg) initially followed by a continuous dose of 0.3–0.6 mg/kg.Oxycodone (0.1 mg/kg) 30 minutes before the cessation of the procedure.Rocuronium if train-of-four is 0–1.Remifentanil (0.15 μg/kg).

Dexamethasone and NSAID will be omitted. The total dose of anaesthetics is continuously recorded.

#### Postoperative management

Paracetamol 1 g × 4.Oxycontin 5–10 mg × 2.Oxynorm 5–10 mg × 2 (pro necessaire).Ondansetron 4 mg (pro necessaire).

### Outcomes

**Primary endpoint**:Levels of systemic inflammatory response expressed by serum C-reactive protein (CRP) and interleukin 6 (IL-6) measured postoperatively day one to day three**Secondary endpoints** Levels of systemic inflammation in serum expressed by: Eotaxin, Eotaxin-3, granulocyte–macrophage colony-stimulating factor (GM-CSF), interferon-gamma (IFN-γ), interleukin 1 alpha (IL-1α), interleukin 1 beta (IL-1β), interleukin 2 (IL-2), interleukin 4 (IL-4), interleukin 5 (IL-5), interleukin 7 (IL-7), interleukin 8 (IL-8), interleukin 10 (IL-10), interleukin 12 (IL-12), interleukin 23 (IL-23), interleukin 13 (IL-13), interleukin 15 (IL-15), interleukin 16 (IL-16), interleukin 17a (IL-17A), interferon gamma-induced protein 10 (IP-10), monocyte chemoattractant protein 1 (MCP-1), monocyte chemoattractant protein 4 (MCP-4), macrophage derived chemokine (MDC), macrophage inflammatory protein 1 alpha (MIP-1α), macrophage inflammatory protein 1 beta (MIP-1β), thymus and activation regulated chemokine (TARC), tumor necrosis factor alpha (TNF-α), tumor necrosis factor alpha (TNF-β) lymphotoxin alpha (LT-α), vascular endothelial growth factor A (VEGF-A) and interleukin 1 receptor antagonist (IL-1RA) measured on the first three postoperative days.Postoperative surgical and medical complications (30 days) according to Clavien-Dindo classification [27] and Comprehensive Complication Index [28].Postoperative dynamic pain registration (visual analog scale (VAS)) at rest twice daily (morning and evening) and registration of opioid consumption in medical charts.Intraoperative blood loss (mL).Conversion rate to open surgery.Total surgical duration (minutes).Total anaesthesia duration (minutes).Lymph node yield.Length of hospital stay (hours/days).Time to passage of flatus (hours).Time to passage of stool (hours/days).

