### Participant timeline, data collection and follow-up

The preoperative assessment will consist of information concerning baseline data (age, gender, body-mass index (BMI), ASA-score, Charlson Comorbidity Index (CCI), WHO performance status, date of diagnosis, type of planned operation, date of randomization and operation (Figs. 1 and 2). Patients will be preoperatively asked to fill out the QoR-15 questionnaire at baseline and from the first until the third postoperative day [29]. A full recovery status (QoR-15) will be collected 14 days postoperatively.

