### Sample size

The Monte Carlo method calculated the power of the mixed effect model used for the log-normal distributed outcome of C-reactive protein (CRP) levels. The sample size calculation was based on the primary outcome (the systemic inflammatory postoperative response expressed by pro-inflammatory and anti-inflammatory cytokines). It was assumed that the CRP level in the group of patients undergoing laparoscopic surgery for colorectal cancer would be 19% higher than patients with robot-assisted surgery, with an interpersonal variation of 0.63 and an intrapersonal variation of 0.34 for the logarithmic transformed CRP. The mixed-effect model was adjusted for type of operation and time. The assumption of CRP among elective malignant colonic resections was based on postoperative measurements on days 1–3 from an observational data set of 298 patients undergoing surgery for colorectal cancer using robot-assisted or laparoscopic methods from 2017 to 2019 at our surgical department, Hospital Sønderjylland, University Hospital of Southern Denmark  [17]. To obtain a power of 86% and an alpha level of 0.05 for a two-sided p-value, we aimed to include a minimum of 42 patients.

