### Statistics

Descriptive statistics will be utilized to check for exchangeability between the two groups according to baseline variables. Categorical variables will be analyzed with a Chi-square or Fischer’s exact test depending on Cochran’s rule. Continuous and discrete variables will be analyzed with an unpaired t-test or Wilcoxon rank-sum test depending on the distribution of the variables. The primary, secondary and exploratory endpoints will also be compared using descriptive statistics. For continuous and discrete variables, repeated measurement ANOVA or Kruskal–Wallis rank-sum tests will be used to compare these variables across timepoints stratified according to the operation method. The normality and heterogeneity of variance assumptions for the t-test and the ANOVA will be graphically assessed using quantile–quantile plots. A mixed-effect model will be utilized to analyze the degree of systemic and peritoneal inflammatory response because of repeated measurements. Logistic regression will be utilized to analyze perioperative complications, 30-day mortality, surgical and medical complications. Odds ratios with 95% confidence intervals will be reported. A poisson or linear regression will be used for time from treatment start until end, and the Quality of Recovery questionnaire (QoR-15 score). Quantile–quantile plots will be used to check if the deviance and the Pearson residuals are normally distributed, and a scatterplot of the deviance and Pearson residuals will check the closeness of the model to our data. If the residuals for the mixed-effect model are not normally distributed, a log transformation of the outcome may be necessary. If the residuals are still not normal distributed, a mixed-effect gamma model will be performed. If these residuals are not normally distributed, logistic regression with another type of link function will be utilized. If deviance residuals are not normally distributed and are not close to zero for the poisson regression, a negative binomial regression or linear regression with bootstrapped confidence intervals will be utilized. If adjustments in the mixed-effect model are necessary, a univariate analysis with only the exposure variable will be included as a sensitivity analysis. If the negative binomial regression is utilized, a poisson regression will be added as a supplementary analysis. No subgroups analysis will be a part of this project. All regression analyses will follow the one-in-ten rule to avoid overfitting. No interim analyses will be performed as no similar prospective randomized clinical trial has previously been performed, so completion of this study is of great importance.

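### The primary comparison uses postoperative CRP and IL-6 levels without a preoperative value as covariate, which costs precision but does not bias the randomised comparison

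*Protocol article*

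**What the plan says.** The Background section of the protocol article gives the aim: "This study aims to evaluate the systemic and peritoneal inflammatory stress response induced by robot-assisted surgery compared with laparoscopic surgery". Under Outcomes, the primary endpoint is "Levels of systemic inflammatory response expressed by serum C-reactive protein (CRP) and interleukin 6 (IL-6) measured postoperatively day one to day three". Neither there nor in the abstract is it defined as a change from, or a value adjusted for, a preoperative measurement.

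The section on participant timeline and data collection lists the baseline data: "The preoperative assessment will consist of information concerning baseline data (age, gender, body-mass index (BMI), ASA-score, Charlson Comorbidity Index (CCI), WHO performance status", followed by dates and the planned operation. CRP and IL-6 are not in the list. The exploratory questionnaire QoR-15, by contrast, is explicitly collected at baseline. The same section refers to Figs. 1 and 2, which are not available here.

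Two passages bear on adjustment. Under Sample size: "The mixed-effect model was adjusted for type of operation and time". Under Statistics: "If adjustments in the mixed-effect model are necessary, a univariate analysis with only the exposure variable will be included as a sensitivity analysis". The second makes adjustment conditional and names no covariate.

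**The concern.** The aim concerns the response that surgery provokes, while the endpoint is the marker level afterwards. Patients with T1 to T4a tumours and ASA scores up to 3 may come to surgery with different degrees of inflammation. To the extent that these differences persist into days 1 to 3, they add to the between-patient variance, which dominates the error of the arm comparison. A preoperative value of the same marker is an obvious covariate for removing part of it.

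Two things are at stake: the width of the confidence interval, and the ability to see and correct a chance difference in preoperative inflammation between two arms of 25. An analysis plan can add a covariate later, but it cannot recover blood that was never drawn before incision.

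**Working it through.** **Inputs.** From Sample size: laparoscopic CRP "would be 19% higher than patients with robot-assisted surgery", so the target is ln(1.19) = 0.174; and "an interpersonal variation of 0.63 and an intrapersonal variation of 0.34 for the logarithmic transformed CRP". The text does not say whether 0.63 and 0.34 are standard deviations (SDs) or variances; they are read as SDs here. Three samples per patient are assumed, since the planning data were "based on postoperative measurements on days 1–3 from an observational data set of 298 patients". From Recruitment, randomization and blinding: 25 per arm, allocated 1:1. The correlation r between preoperative log CRP and a patient's postoperative mean is not given and is assumed. No variance is given for IL-6, so the arithmetic covers CRP only.

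**1. The plan's own figure.** With 21 per arm, a comparison of patient means (equivalent to the balanced mixed model) has 13.4% power by formula and 13.0% by simulation, against the stated 86% for 42 patients. Reading the inputs as variances gives 9.6%. The two-sided calculations with 42 patients in total that come close leave out the between-patient variation: 81.9% with ln(1.19) and 88.0% with 0.19. That is a separate issue.

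**2. Standard error (SE) without baseline.**
- Variance of a patient's three-day mean: 0.63² + 0.34²/3 = 0.397 + 0.039 = 0.435 (unrounded terms), SD 0.660.
- Between-patient share: 0.397/0.435 = 91%.
- SE of the arm difference: √(2/25 × 0.435) = 0.187.
- 95% interval: a factor of exp(1.96 × 0.187) = 1.44 either way.

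**3. SE with the log preoperative value as covariate.** The SE is multiplied by √(1 − r²), and the equivalent sample size is 50/(1 − r²). These proportional gains do not depend on the SD or variance reading. Power is for a 19% effect with 50 patients.

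| r (assumed) | SE | Equivalent N | Power |
|---|---|---|---|
| 0 | 0.187 | 50 | 15.2% |
| 0.3 | 0.178 | 55 | 16.3% |
| 0.5 | 0.162 | 67 | 18.8% |

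Put the other way, omitting baseline makes the SE 5% larger at r = 0.3, 15% at 0.5 and 40% at 0.7. Even at r = 0.8, power with 50 patients is only 34.2%.

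**4. Bias and type I error.** In simulations with 25 per arm and r from 0.3 to 0.7, the postoperative-only comparison returned mean estimates of 0.173 to 0.175 for a true 0.174. It rejected a true null in 5.1% to 5.3% of trials, against 5.1% to 5.2% with the covariate. Simulated power with the covariate was 15.5%, 18.2% and 23.4% at r = 0.3, 0.5 and 0.7, against 14% to 15% without. The first two are slightly below the table's figures.

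**5. Chance imbalance.** A baseline imbalance of one standard error shifts the unadjusted contrast by r × 0.187: 0.056 log units at r = 0.3 and 0.093 at r = 0.5, or 32% to 54% of 0.174. The chance that this shift alone reaches 0.174 in either direction is about 0.2% at r = 0.3 and 6% at r = 0.5.

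**6. Change score.** With equal SDs before and after surgery, the variance of the change is 2(1 − r) times that of the level, so it is larger whenever r < 0.5. Power with 50 patients is 12.1% at r = 0.3 and 15.2% at r = 0.5, below the covariate model in both cases.

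**The case against.** The strongest reply is that the trial compares two operations under 1:1 randomisation. Preoperative inflammation is balanced in expectation, so the difference in postoperative log level estimates the difference in response. This stands. A reader might infer from the gap between aim and endpoint that pre-existing inflammation is mistaken for surgical stress; as a claim of bias in the arm comparison, the documents do not support it.

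A reader might also infer that a chance baseline difference could readily pass for the 19% effect. If preoperative log CRP has an SD of 0.8 to 1.2 (assumed), arms of 25 would differ by more than 0.2 log units (22%) in 38% to 56% of trials. But a baseline difference carries over only through the slope r × 0.66/SD of baseline. For r of 0.3 to 0.5 that is 0.165 to 0.41, so 0.2 log units at baseline moves the result by only about 3% to 9%. The confidence interval already allows for such chance shifts.

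The third reply is that Fig. 1 is missing, so a preoperative sample cannot be ruled out, and that a condensed article may leave covariates to the analysis plan. The sentence under Sample size describes the power model, and the Statistics section leaves adjustment open. This too stands in part: the documents do not show that no sample is taken. It does not dispose of the point, because the endpoint and the visible baseline list are set out here without the marker, and no later plan can supply an undrawn sample.

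Finally, the exclusion of emergency surgery, metastatic disease, inflammatory bowel disease, immunomodulatory treatment and daily NSAID use removes some sources of preoperative variation. The correlation may therefore be modest.

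**Conclusion.** The point holds as one of efficiency. As described, the primary comparison leaves differences in preoperative CRP and IL-6 in the residual variance, and nothing in the visible text provides the value needed to remove them. For CRP, adjustment would reduce the standard error from about 0.187 to between 0.178 and 0.162, if the correlation is 0.3 to 0.5, the stated variations are SDs and each patient has three samples. At zero correlation there is no gain. Validity is not in question: the contrast is unbiased and type I error is near 5%. Nor does the change restore the stated 86% power.

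**What to change.** Under Outcomes and in the list of baseline data, name CRP and IL-6 from blood drawn before incision, unless Fig. 1 already schedules that sample. In Statistics, prespecify the log preoperative value of the same marker as a fixed covariate in the primary mixed model, with days 1 to 3 as the outcome and the arm effect over those days as the estimate. State this unconditionally, so that adjustment does not depend on a later judgement of need. Do not use a change score.

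The cost is at most one extra tube and one extra assay time point per patient, plus one model degree of freedom. This assumes that blood is drawn before surgery anyway, which the visible text does not say. If the sample is already scheduled, naming it and adding the model sentence is enough.

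### CRP and IL-6 are both primary, but the single 5% alpha and the 86% power describe a decision on CRP alone, and no success rule links the two markers

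*Protocol article*

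**What the plan says.** - **Outcomes, primary endpoint:** "Levels of systemic inflammatory response expressed by serum C-reactive protein (CRP) and interleukin 6 (IL-6) measured postoperatively day one to day three". The Methods part of the abstract names the same pair: "serum C-reactive protein (CRP) and interleukin 6 (IL-6) levels between postoperative days one and three". Neither place states a success rule, an order or a split of alpha.
- **Sample size, marker powered:** "The Monte Carlo method calculated the power of the mixed effect model used for the log-normal distributed outcome of C-reactive protein (CRP) levels". The effect (19% higher with laparoscopy) and both variance components are for CRP. IL-6 has no effect size, variance or power.
- **Sample size, error rate and number:** "an alpha level of 0.05 for a two-sided p-value", with 86% power; "we aimed to include a minimum of 42 patients". Recruitment, randomization and blinding sets the target at 50, 25 per arm.
- **Sample size, name of the primary outcome:** "systemic inflammatory postoperative response expressed by pro-inflammatory and anti-inflammatory cytokines".
- **Statistics:** a mixed-effect model is assigned to the systemic and peritoneal inflammatory response. The section also says: "The primary, secondary and exploratory endpoints will also be compared using descriptive statistics". It lists t-test or Wilcoxon comparisons for continuous variables, and repeated-measures ANOVA or Kruskal–Wallis tests across timepoints, stratified by operation method.

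**The concern.** An alpha and a power figure mean something only in relation to a rule for declaring success. Here the endpoint has two components and the calculation has one. A trial that reports a CRP difference without an IL-6 difference, or the reverse, could be written up as positive or negative, and the protocol would not settle which. Choosing the favourable marker afterwards would look compliant with the protocol while running at more than 5%. Requiring both would keep the error rate but would not carry the advertised power.

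The Sample size wording adds a third description of the primary outcome. The Background section classes CRP as an acute phase reactant, not a cytokine, and the Outcomes section places the wider cytokine panel among the secondary endpoints. Read literally, that sentence matches neither the endpoint as defined nor the marker that was powered.

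**Working it through.** **Inputs from the protocol article.** Two primary markers (Outcomes); two-sided alpha 0.05, 86% power, N = 42, CRP ratio 1.19, between-patient variation 0.63 and within-patient variation 0.34 on the log scale (Sample size); N = 50 planned (Recruitment, randomization and blinding).

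**Assumption.** The correlation r between the CRP and IL-6 test statistics is not given, so a range of 0 to 0.9 is used. The Background describes cytokine release leading to production of acute phase reactants such as CRP, which makes a positive r plausible but does not fix it.

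**Step 1. The plan's own power figure.** Read 0.63 and 0.34 as standard deviations and take each patient's mean of three log-CRP values:
- SD = √(0.63² + 0.34²/3) = √(0.3969 + 0.0385) = 0.660
- difference = ln 1.19 = 0.174
- SE with 21 per arm = 0.660 × √(2/21) = 0.204
- power ≈ Φ(0.174/0.204 − 1.96) = Φ(0.854 − 1.960) = 13.4%

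The 86% is not reproduced. Reading the components as variances gives 9.6%. This is a separate matter from multiplicity. It matters here only because 86% cannot be used as a firm base for joint-power figures.

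**Step 2. Success if either marker differs, each tested at 5%.** The family-wise error is 1 − P(|Z₁| < 1.96 and |Z₂| < 1.96), with (Z₁, Z₂) bivariate normal. At r = 0 this is 1 − 0.95² = 9.75%.

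| Assumed r | Either marker significant | Both significant (no effect on either) |
|---|---|---|
| 0 | 9.75% | 0.25% |
| 0.5 | 9.07% | 0.93% |
| 0.7 | 8.35% | 1.65% |
| 0.8 | 7.81% | 2.19% |
| 0.9 | 7.04% | 2.96% |

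The two columns sum to 10%, because P(either) = 5% + 5% − P(both).

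**Step 3. Success only if both markers differ.** A false claim needs a rejection on at least one marker with no true difference, so its probability is at most 5% whatever r is. Power satisfies P(both significant) ≤ P(CRP significant). It therefore cannot exceed the CRP-only figure, and equals it only if IL-6 is significant whenever CRP is. A number would need an IL-6 effect and variance, and the document has neither.

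**Step 4. CRP first, IL-6 only if CRP succeeds.** If CRP has no true difference, any false claim requires a false CRP rejection: at most 5%. If CRP has a true difference and IL-6 has none, a false claim requires a false IL-6 rejection at 5%: again at most 5%. CRP keeps the full alpha used in the calculation.

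**Step 5. Comparison: 0.025 for each marker.** Take 86% at face value. The implied standardized effect is 1.960 + 1.080 = 3.040, and CRP power at N = 42 becomes Φ(3.040 − 2.241) = 78.8%. At N = 50 it is Φ(3.040 × √(50/42) − 2.241) = 85.9%. A split therefore uses up the margin between 42 and 50; the ordered test does not.

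**The case against.** The strongest reply is that the document never says either marker is enough. Both statements of the endpoint join CRP and IL-6 with "and". If that means both must differ, there is no inflation at all. That stands as far as it goes: a reader might infer that the false-positive rate is about double the stated 5%, and the document does not support this as a fact. Doubling is close to the ceiling and needs both an unstated either-marker rule and weak correlation. The reply does not close the gap, though. The word is equally compatible with two separate endpoints, and a both-markers rule would leave the power statement describing something else.

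A reader might also infer that each marker gets several confirmatory tests, by method or by day. The Statistics section does not support that. It assigns the mixed model to the inflammatory response, and that is the model the sample size uses. The t-test and Wilcoxon test are alternatives chosen by distribution, and the additional comparison of the endpoints is labelled descriptive. The ANOVA and Kruskal–Wallis tests compare timepoints stratified by operation method and are most naturally read as within-arm comparisons. What remains is that no one sentence names the decisive contrast.

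Nor does the document assign an uncorrected 5% to the 29 secondary serum cytokines. Its only alpha sits in the sample size calculation, and multiplicity for a secondary panel is commonly left to an analysis plan.

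Finally, an analysis plan that is not shown may set the rule for the primary markers. That is possible, but the mismatch between endpoint, power calculation and primary-outcome wording lies within the text that is present.

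**Conclusion.** The concern holds in this form: the primary endpoint has two markers, the alpha and power belong to one, and the Sample size section describes the primary outcome in a third way. The primary error rate is therefore not fixed by this document.

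- If either marker suffices at 5% each: about 7% to 9.75%, assuming r between 0.9 and 0.
- If both are required: at most 5%, with power at or below the CRP-only figure by an amount that cannot be calculated.

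The error rates rest on normal test statistics and the assumed correlation range. They do not depend on whether the 86% is correct. The change should be made before unblinding.

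**What to change.** 1. In Outcomes and Statistics, name log CRP over postoperative days 1 to 3, analysed by the arm contrast of the mixed-effect model already assigned, as the first and only unconditional confirmatory test at two-sided 5%.
2. Test IL-6 at two-sided 5% with the same model and contrast only if CRP is significant. Otherwise report it as an estimate with a confidence interval and no claim.
3. State that the t-test/Wilcoxon and ANOVA/Kruskal–Wallis comparisons of these two markers are descriptive.
4. In Sample size, replace the pro- and anti-inflammatory cytokine wording so that it matches the Outcomes section, and say that the calculation covers CRP, the first test in the order.

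Requiring both markers, Holm's procedure or 0.025 each would also settle the rule. The ordered test fits best because CRP is the marker that was powered and it keeps its full alpha.

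Cost: a few sentences and no extra patients. The downside is that IL-6 cannot be claimed if CRP fails.
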